Many women experience changes loss of muscle mass as part of the normal aging process [25]. However, there are several key unanswered questions about whether postmenopausal cancer survivors experience greater declines in muscle mass compared to women without a history of cancer. If yes, do they undergo an accelerated aging trajectory, with a different slope and quicker progression to functional impairment and disability? This protocol will describe the design of a prospective longitudinal study using the D_3_Cr method to measure muscle mass in postmenopausal cancer survivors and a comparison group of women without a cancer history (“non-cancer controls”). Both cancer survivors and cancer-free controls are drawn from the same source population, the Women’s Health Initiative (WHI).The specific objectives of this project are to: 1) develop age-standardized percentile curves to characterize the distributions of D_3_- muscle mass in cancer survivors and cancer-free controls, 2) examine whether the associations between muscle mass, physical function, and functional decline differ in cancer survivors and cancer-free controls, and 3) create multivariate risk-prediction algorithms to detect low muscle mass in cancer survivors and cancer-free controls. We hypothesize that cancer survivors will have lower muscle mass and experience accelerated decline in physical function compared to cancer-free controls.

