## Materials and methods

### Study population

The [name] study (**M**u**s**cle mass in the **Li**fe and **L**ongevity **A**fter **C**ancer cohort) will include approximately 6000 postmenopausal women. Participants will be recruited from the ongoing Women’s Health Initiative (WHI) study cohort. The WHI is a prospective longitudinal study focused on examining causes of morbidity and mortality in postmenopausal women.

All [name] participants have been active participants in the WHI study since the 1990s. Postmenopausal women aged 50–79 years enrolled in the WHI clinical trials and observational study between 1993 and 1998 at 40 clinical centers across the U.S. (n = 161,808) [26]. Over the past thirty years, follow-up has been consistent and is still ongoing. In the initial phase of the WHI (up to 2005), participants visited clinical centers for in-person measurements, including anthropometric measurements. Since then, the WHI has collected comprehensive annual questionnaires on medical history, demographics, and lifestyle characteristics via mail, online surveys and telephone [27].

For [name], we will recruit women who are actively still participating in the WHI and have recently completed an in-home study funded by the WHI. The sample size for [name] is limited to all women who have completed the WHI home visit, as the home visit will provide important information on measured covariates (i.e., body weight, blood-based biomarkers, measures of physical function). The study population is depicted in Fig 1. Cancer survivors will be recruited from a WHI sub-cohort called the Life and Longevity After Cancer (LILAC) study. Postmenopausal women with no cancer history (“non-cancer controls”) will be recruited from a WHI sub-cohort called the Long Life Study 2 (LLS2), a minority enriched sub-cohort of women [28, 29]. The WHI is currently completing in-home study visits for LILAC and LLS2 participants. Home visits consist of anthropometric measures (e.g., height, weight, blood pressure), assessment of physical function via the short physical performance battery (SPPB), and a fasting venous blood draw [30].

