*Aim 2*. To examine the association between D_3_Cr muscle mass and functional outcomes in cancer survivors and non-cancer controls, we will use data on physical performance (SPPB) and muscular strength (grip strength) from the WHI home visits. We hypothesize that cancer survivors will have worse physical function than non-cancer controls and will also experience greater decline in physical function over time. We will first investigate the cross-sectional joint distribution of D_3_Cr muscle mass, muscle strength, and physical function for cancer survivors and non-cancer controls. Muscle strength will be measured using handheld dynamometer (Jamar hand dynamometer; Lafayette Instruments, Lafayette, IN). Participants are instructed to squeeze the handle of the dynamometer as hard as possible for two trials per hand. Physical function is being measured via the Short Physical Performance Battery (SPPB), a validated test of physical function consisting of three tests: balance, gait speed, and chair stands. Short physical performance battery scores range from 0 to 12, with higher scores indicating better physical function. Multivariate adjusted linear regression models will be used to calculate means and 95% confidence intervals of muscle mass by SPPB score (0–12), timed walk (meters/second), number of chair stands, and grip strength (kg). These models will include a product interaction term (muscle mass x cancer survivorship status) to separately estimate these relationships among cancer survivors and non-cancer controls [38–40]. Among cancer survivors, we will examine effect heterogeneity by time since diagnosis, cancer site, and treatment modality by including product interaction terms in our fully adjusted regression models (i.e., to control for potential confounding by health or lifestyle related characteristics).

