We will use annual WHI questionnaires measuring activities of daily living as the outcome in a longitudinal analysis of the relationship between baseline muscle mass and functional decline over time. Activities of daily living and instrumental activities of daily living will be measured using a validated questionnaire (RAND-36). In this analysis, we will use linear mixed effects models to examine the relationship of interest while accounting for correlation between outcomes measured on the same individual [41–43]. The model will include: year, where the coefficient represents the change in functional status per year (slope); cancer survivorship status (1 if cancer survivor, 0 if non-cancer control), where the coefficient represents the difference in mean functional status at baseline after accounting for baseline muscle mass; and a product interaction term between year and survivorship status. The interaction term can be interpreted as the difference in outcome time trend (i.e., slope) between cancer cases and non-cancer controls and will enable assessment of effect modification of the change in functional status by cancer survivorship status after accounting for baseline muscle mass. Models will be adjusted for relevant demographic and cancer-related confounding variables. Moreover, we will examine potential interaction muscle mass (at baseline) and year, to understand whether there is a difference in the slope of functional decline for each additional unit of muscle mass. This will elucidate whether there is evidence of effect modification of the change in functional decline over time by baseline muscle mass. In this analysis, we will assume linear effects but will empirically examine this assumption and employ appropriate statistical tools if evidence of non-linearity is found.

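### Aim 2 cross-sectional models: adjacent sentences make muscle mass both the response and part of the interaction term, so the stated term cannot test whether the muscle–function association differs by cancer status

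*Protocol article*

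**What the plan says.** Protocol article, Background: the second objective is to "examine whether the associations between muscle mass, physical function, and functional decline differ in cancer survivors and cancer-free controls".

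Protocol article, Statistical plan, Aim 2, makes three statements about the cross-sectional step:

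- The lead-in puts function on the outcome side: "To examine the association between D_3_Cr muscle mass and functional outcomes in cancer survivors and non-cancer controls".
- The model sentence puts muscle mass on the outcome side: "Multivariate adjusted linear regression models will be used to calculate means and 95% confidence intervals of muscle mass by SPPB score", and likewise by timed walk, chair stands and grip strength.
- The interaction sentence refers back to those same models: "These models will include a product interaction term (muscle mass x cancer survivorship status) to separately estimate these relationships" in the two groups.

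No function measure x survivorship status term is named. The longitudinal step that follows has clear roles: "We will use annual WHI questionnaires measuring activities of daily living as the outcome in a longitudinal analysis", with baseline muscle mass as a covariate.

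**The concern.** A model that yields mean muscle mass by SPPB score has muscle mass as its dependent variable. An interaction of muscle mass with survivorship status belongs in a model where muscle mass is a predictor. The text puts both into one set of models.

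At stake is the part of the second objective that asks whether the association between muscle mass and function differs by cancer status. The longitudinal mixed model lists year x status and muscle mass x year, but no muscle mass x status term. The cross-sectional product term is therefore the only one the article describes for that question, and the problem applies to all four function measures. The planned interactions by time since diagnosis, cancer site and treatment among survivors use the same regression models, so they inherit the uncertainty about which variable is the response.

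**Working it through.** The article gives no effect size, power or test level for this analysis, so there is no figure to reproduce. The check is algebra plus a simulation.

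**Notation.** M = muscle mass, F = a function measure, C = 1 for survivors and 0 for controls.

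**Inputs.** From the document: n = 6000 ("will include approximately 6000 postmenopausal women"). Assumed: half are survivors; M has SD 1 and is 0.2 SD lower in survivors; F has slope 0.3 on M in controls and 0.3 + d in survivors, with d = 0, +0.1 or -0.3; error SD is 1; tests are two-sided at 0.05; 500 replicates.

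**1. Literal model: M = a + bF + cC + g(M x C).** One coefficient b serves both groups.

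- Survivors: the part left to explain is (1 - g)M - bF. With F = (0.3 + d)M + e, least squares gives g = 1 - b(0.3 + d) and leaves the residual -be.
- Controls: the residual variance is 1 - 2(0.3)b + 1.09b², because var(F) = 0.3² + 1 = 1.09.
- With equal groups, minimising 1 - 0.6b + 1.09b² + b² gives b = 0.3/2.09 = 0.144.

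| d | g = 1 - 0.144(0.3 + d) | g, simulated mean | b, simulated mean | Product term significant |
|---|---|---|---|---|
| 0 | 0.957 | 0.956 | 0.144 | 100% |
| +0.1 | 0.943 | 0.943 | 0.143 | 100% |
| -0.3 | 1.000 | 1.000 | 0.143 | 100% |

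The product coefficient stays near 1 because in survivors the product is the response. Its small shortfall from 1 depends on the survivor slope and the shared b, not on the difference between groups. A test of g = 0 rejects whether or not the slopes differ.

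The survivor residual SD is |b| x 1 = about 0.14, small against a muscle-mass SD of 1 but not zero.

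The survivor share is an assumption. For a share p, b = 0.3(1 - p)/[1.09(1 - p) + p]. At p = 0.3, b = 0.21/1.063 = 0.198 and, with d = 0, g = 0.941. At p = 0.7, b = 0.09/1.027 = 0.088 and g = 0.974. The conclusion does not change.

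**2. Literal model plus a muscle-mass main effect.** M is regressed on itself. The coefficient on M is 1, all others are 0, and the largest residual is about 1e-14 (rounding error). Function drops out.

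**3. Aligned models.** Share of replicates with a significant interaction:

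| d | F on M, C, M x C | M on F, C, F x C |
|---|---|---|
| 0 | 5.0% | 6.2% |
| +0.1 | 98.4% | 86.4% |
| -0.3 | 100% | 100% |

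The Monte Carlo standard error at 5% is √(0.05 x 0.95/500) = about 1.0 percentage point, so both aligned models are compatible with the nominal level.

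**4. The two repairs are not interchangeable.** The slope of M on F is βσ²/(β²σ² + 1), where β is the slope of F on M and σ² the variance of M. With β = 0.3 in both groups and σ² = 1, it is 0.3/1.09 = 0.275 in each. If the survivor SD were 1.2 (an assumption for illustration), the survivor value would be 0.432/1.1296 = 0.382 although the slopes of F on M are still equal. Which response is chosen can therefore decide whether a difference is found.

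**The case against.** The strongest defence is that the intent is plain. The interaction sentence says the relationships are to be estimated separately in the two groups. The lead-in and the longitudinal model both treat function as the outcome, and with function as response the stated interaction is correct. One phrase is then miswritten, and an analyst would notice the response among its own predictors on fitting the model. A silently wrong result is unlikely. This stands, and it lowers the severity. It does not remove the contradiction, because the article does not settle which sentence is wrong.

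Two stronger readings are tempting, and the documents support neither:

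- **That survivors are fitted with zero residual in the literal model.** The function coefficient is shared with controls and is not zero, so survivor residuals have SD about 0.14 in the setting above. The fit is exact only if a term the text does not name, such as a muscle-mass main effect, is added.
- **That keeping muscle mass as the response answers the wrong question.** The Background objective is about whether associations differ, which is symmetric, and the cross-sectional step is introduced as a joint distribution. Modelling muscle mass by function level, with function x status, is a legitimate way to compare an association between groups. The wording elsewhere favours function as response but does not make the other direction an error.

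**Conclusion.** The concern holds as a contradiction between adjacent sentences about the response variable. Taken literally, the product term is significant in 100% of simulated replicates with a coefficient of 0.94 to 1.00, whatever the true slope difference, so it gives no test of whether the muscle–function association differs by cancer status. That the response sits inside its own predictor follows from the wording alone. The sizes quoted depend on the assumed slopes, error SD and survivor share.

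This is not detail left to an unseen analysis plan: the article states both the quantity to be estimated and the interaction term, and they do not fit together. A reader might infer that Aim 2 as a whole is invalid. It is not, because the longitudinal model has consistent roles for its variables and is unaffected. The point should be corrected before analysis, but it is below a must-fix.

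**What to change.** Name one response before the data are analysed and match the interaction to it. Either specification is acceptable:

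1. Response: SPPB, gait speed, chair stands or grip strength, one model each. Predictors: muscle mass, survivorship status, muscle mass x status, covariates. This fits the Aim 2 lead-in and the longitudinal model.
2. Response: muscle mass. Predictors: the function measure, survivorship status, function measure x status, covariates, with one model per function measure.

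In either case report the slope in survivors, the slope in controls, and their difference with a 95% CI. Use the same response in the survivor-only interactions by time since diagnosis, cancer site and treatment. If option 1 is chosen and adjusted mean muscle mass by SPPB score is still wanted, present it as a separate descriptive table, with function measure x status as its interaction.

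Cost: two sentences of wording and no new data.

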Research is urgently needed to study older cancer survivors as they represent a growing segment of the population. Given increasing rates of cancer survivorship, and increasing life expectancies (in women in particular), the number of older female cancer survivors is rising [13]. Research focused on muscle mass in older women is particularly relevant because, on average, postmenopausal women lose 1–3% of muscle mass and strength per year [14]. Although muscle mass is recognized as an important predictor of morbidity and mortality in older adults, measurement of muscle mass in large-scale population health and epidemiologic research remains a challenge [15–17]. Imaging modalities (e.g., DXA, CT, MRI) exist for measurement of muscle mass in clinical settings and can be used for diagnostic purposes or clinical research studies [18]. However, there are numerous barriers to implementation of these measurement approaches in population health research, including cost, accessibility, staffing needs, and for CT scans, radiation exposure.

Recently, the creatine dilution (D_3_Cr) method has gained popularity as a measure of muscle mass in large-scale, population-based research studies [19, 20]. The D_3_Cr method is a simple, inexpensive, and non-invasive assessment that can be used to measure muscle mass remotely in a community dwelling population of postmenopausal women. It has been validated through rigorous laboratory and clinical testing and previously used in clinic-based epidemiology research [19, 21, 22]. Cross-sectional and longitudinal validation studies have been performed in rodents [23] and humans [24]. Dilution of a stable isotope-labeled creatine, and measure of urinary creatinine enrichment provides a direct measure of whole body creatine pool size which is proportional to total body muscle mass [21].

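### No confounder-by-year term is stated in the Aim 2 longitudinal model, so on its natural reading neither slope contrast is adjusted for age or race/ethnicity differences in decline

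*Protocol article*

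**What the plan says.** The longitudinal part of Aim 2 (Protocol article, Statistical plan) relates baseline D3-creatine muscle mass to annual questionnaire measures of function: "we will use linear mixed effects models to examine the relationship of interest while accounting for correlation between outcomes measured on the same individual". The stated terms are year, survivorship status and "a product interaction term between year and survivorship status". The last is read as the difference in slope between survivors and controls once baseline muscle mass has been taken into account.

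A year by baseline muscle mass interaction comes afterwards, as a possible further term, "to understand whether there is a difference in the slope of functional decline for each additional unit of muscle mass". Other covariates get one sentence: "Models will be adjusted for relevant demographic and cancer-related confounding variables". That paragraph does not name age or race/ethnicity. It states no product of a confounder with year and excludes none.

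Two statements elsewhere bear on confounding. The Background says that "postmenopausal women lose 1–3% of muscle mass and strength per year". The Study population section describes the control source, the Long Life Study 2, as "a minority enriched sub-cohort of women".

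**The concern.** Both questions in this analysis concern slopes. A baseline covariate entered only as a main effect moves a woman's whole trajectory up or down by a constant. It says nothing about how fast she declines, so it removes no confounding from a comparison of rates of decline.

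Three consequences follow if the model is fitted as written:

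- **Year by muscle mass.** Women with low muscle mass will tend to be older. If older women decline faster, this term picks up the age effect even when muscle mass has no effect on the slope. No imbalance between survivors and controls is needed.
- **Year by survivorship.** If survivors and controls differ in age or race/ethnicity mix, and decline varies with either, the term is biased. The direction depends on which group is older or has more of the faster-declining women, so the bias can create an apparent acceleration in survivors or hide a real one.
- **The claim of accounting for muscle mass.** Until muscle mass is allowed to affect the slope, the survivorship slope difference is not net of it.

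At stake is whether faster decline is attributed to cancer or muscle mass when age or population mix explains it, or is missed when it is real.

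**Working it through.** The article gives no power, error rate or effect size for this analysis, so there is no planned figure to reproduce. The check has three parts.

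**1. What the slope terms estimate.** Let woman i have true slope b0 + b1·S + b2·M − g·A, with S survivorship, M baseline muscle mass and A age. With balanced annual data, a model with A as a main effect only gives the same slope contrasts as regressing each woman's own slope on the terms that multiply year. Hence:

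- With year by S only, the coefficient estimates b1 + b2·(difference in mean M) − g·(difference in mean age). The b2 part stays although M is a main effect. The article hypothesizes lower muscle mass in survivors, so on its own expectation the difference in mean M is not zero.
- With year by M (per SD) and b1 = b2 = 0, the coefficient estimates −g·r·SD(age), where r is the correlation of mass with age. This is positive when r is negative: low mass appears to predict faster decline.

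**2. Size under one set of assumptions.** From the article: "will include approximately 6000 postmenopausal women". Assumed: half are survivors; five annual scores on a 0–100 scale; residual SD 10; random-slope SD 2 per year; age SD 5 years; g = 0.02, 0.05 or 0.10 points/yr per year of age; r = −0.25 or −0.5; age gap between groups 2 years; two-sided 5% test.

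Variance of one woman's fitted slope: 2² + 10²/10 = 14, where 10 is the sum of squared deviations of the five visit times.

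- SE, survivorship slope difference: √(14 × 2/3000) = 0.097.
- SE, muscle slope per SD: √(14/6000) = 0.048.

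Rejection with no true effect of cancer or muscle mass on slope:

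| g | Survivorship, 2-year gap: bias, rejection | Muscle, r = −0.25: bias, rejection | Muscle, r = −0.5: bias, rejection |
|---|---|---|---|
| 0.02 | 0.04, 7% | 0.025, 8% | 0.05, 18% |
| 0.05 | 0.10, 18% | 0.0625, 25% | 0.125, 73% |
| 0.10 | 0.20, 54% | 0.125, 73% | 0.25, over 99% |

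A simulation in the same settings (400 replicates) gave 4–10%, 16–17% and 52–55% for survivorship, and 7–18%, 24–76% and 72–100% for muscle mass. With no age gap the survivorship test stayed at about 5%. Adding age by year brought both tests to 3–7%.

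Masking: a true excess decline of 0.3 points/yr in survivors has z = 0.3/0.097 = 3.1, power 87%. If controls are 2 years older, the estimate shrinks to 0.2 (g = 0.05; power 54%) or 0.1 (g = 0.10; power 18%).

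**3. A second simulation with other assumptions.** A random-intercept, random-slope model was fitted by generalized least squares: N = 6000; 50% or 30% survivors; intercept SD 20, slope SD 1.5, residual SD 10; age SD 5; 300 replicates; Monte Carlo error about ±2.5 points near 5%. Confounders were main effects only, with no true effect.

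| Test | Scenario | Rejection |
|---|---|---|
| Survivorship | equal mean age and race mix | 5–9% |
| Survivorship | 1-year gap, g = 0.05 | 8–12% |
| Survivorship | 2-year gap, g = 0.1 | 52–56% |
| Survivorship | controls 3 years older, g = 0.1 | 85–88% (bias about +0.3/yr, hiding faster decline in survivors) |
| Survivorship | 20 points more minority women among controls, who decline 0.3 or 0.6 points/yr faster | 9–12% or 21–29% |
| Muscle | decline unrelated to age | 4% |
| Muscle | 1% mass loss per year of age; g = 0.02, 0.05, 0.1 | 7%, 32%, 85% |
| Muscle | 3% loss per year, g = 0.05 | 94% |

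With age by year and race by year added, rejection was 4–8% (survivorship) and 3% (muscle), with bias about zero. Muscle mass was simulated as independent of race, so race alone did not disturb the muscle test.

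**The case against.** The strongest reply is that the article never says main effects only. It says models will be adjusted, does not say how, and rules out no product with year; the form of covariates is detail an article may leave to a fuller plan. This stands as a limit on the wording. It does not dispose of the point: the article writes out the slope terms it wants, none is for a confounder, and it calls the survivorship slope net of muscle mass before any year by muscle mass term is present.

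Second, a reader might infer that both slope tests will reject because of age or race. The documents do not support that. Inflation needs decline to vary with the covariate and the covariate to be associated with survivorship or muscle mass. No group ages, race proportions or age-specific rates of decline are given. Entry through a 2012–2013 home visit does not show which group is older. Treating 1–3% loss per year as an age gradient across women is itself an assumption.

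Third, year by muscle mass is introduced as a possible interaction, so calling it a main conclusion would overstate its role.

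Fourth, a reader might extend the criticism to the product terms in the cross-sectional part of Aim 2, where adjustment is described as "i.e., to control for potential confounding by health or lifestyle related characteristics". That parenthesis explains why the models are adjusted. It does not claim that the interaction coefficients are free of confounding, and no calculation here covers them.

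**Conclusion.** The point holds as a conditional one. Followed on its natural reading, the stated model leaves both slope coefficients unadjusted for age or race/ethnicity differences in decline, and its description of the survivorship slope as net of baseline muscle mass is not met unless year by muscle mass is in the same model.

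Year by muscle mass is the more exposed, since the article itself says muscle falls with age. Year by survivorship is exposed only so far as the groups differ; the minority-enriched control source is a reason to expect a difference in race mix, of unknown size.

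The magnitude cannot be fixed from the article. The range from nominal to 94% (over 99% in the most extreme setting of the closed-form check) reflects the assumed age or race effects on decline, group differences and variances. The bias can mask a difference as well as create one. This is worth correcting before analysis, but it is not a flaw that undermines the study.

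**What to change.** In the longitudinal paragraph of Aim 2, state that at least baseline age and race/ethnicity enter both as main effects and as products with year, in the year by survivorship model and in the year by muscle mass model. Interpret the slope terms from those models. Keep year by muscle mass in the model whenever the survivorship slope is described as accounting for baseline muscle mass, or drop that description.

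The cost is a sentence or two and a few model terms, with no new data. Under the assumed settings of the first simulation, standard errors rise by up to about 4% for year by survivorship and 4–16% for year by muscle mass. The formula 1/√(1 − r²) gives 3% and 15% for muscle mass at r = −0.25 and −0.5, in line with that.

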**Methods:**

This study protocol describes the use of a novel method of muscle mass measurement, D3-creatine dilution method (D_3_Cr), in a large sample (n~6000) of community dwelling postmenopausal women from the Women’s Health Initiative (WHI). D_3_Cr will be used to obtain a direct measure of muscle mass remotely. Participants will be drawn from two sub-cohorts embedded within the WHI that have recently completed an in-home visit. Cancer survivors will be drawn from the Life and Longevity After Cancer (LILAC) cohort, and cancer-free controls will be drawn from the WHI Long Life Study 2. The overall objective of this study is to examine the antecedents and consequences of low muscle mass in cancer survivors. The study aims are to: 1) create age-standardized muscle mass percentile curves and z-scores to characterize the distribution of D3- muscle mass in cancer survivors and non-cancer controls, 2) compare muscle mass, physical function, and functional decline in cancer survivors and non- cancer controls, and 3) use machine learning approaches to generate multivariate risk-prediction algorithms to detect low muscle mass.

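### Aim 2, functional decline only: the longitudinal model gives survivors and controls one common muscle mass-decline association, so it cannot estimate the between-group difference that Objective 2 in the Background asks for

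*Protocol article*

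**What the plan says.** The protocol article words the second aim in more than one way.

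- Background, list of objectives: to "examine whether the associations between muscle mass, physical function, and functional decline differ in cancer survivors and cancer-free controls". This is a question about effect modification by cancer status.
- Abstract, Methods: to "compare muscle mass, physical function, and functional decline in cancer survivors and non- cancer controls". This is a comparison of groups.
- Statistical plan, Aim 2, hypothesis: survivors have worse function and "will also experience greater decline in physical function over time". This too is a comparison of groups.

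The analysis has two parts.

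- Cross-sectional (Statistical plan, Aim 2, first paragraph): "These models will include a product interaction term (muscle mass x cancer survivorship status) to separately estimate these relationships among cancer survivors and non-cancer controls".
- Longitudinal (Statistical plan, Aim 2, second paragraph): described as a "longitudinal analysis of the relationship between baseline muscle mass and functional decline over time". The linear mixed model has year, survivorship status "and a product interaction term between year and survivorship status", with baseline muscle mass accounted for. The article reads that interaction as "effect modification of the change in functional status by cancer survivorship status after accounting for baseline muscle mass". It then adds: "we will examine potential interaction muscle mass (at baseline) and year, to understand whether there is a difference in the slope".

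The longitudinal paragraph states no muscle mass by survivorship term, no three-way term and no model fitted separately by survivorship status.

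**The concern.** For decline, the question in the Background concerns a difference between two associations: how strongly baseline muscle mass relates to the yearly change in function in survivors, minus the same quantity in controls. Neither planned slope term is that difference. Year by survivorship compares the groups' slopes at a given muscle mass. Muscle mass by year is one association for everyone.

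If the analysis follows the listed terms, the decline part of Objective 2 ends with a single blended association. A reader could take that as evidence that muscle mass matters equally in both groups, when the model assumed equality and did not test it.

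**Working it through.** The plan gives no figure to reproduce here, and the article states no effect size, variance or group split for Aim 2. The check is algebraic.

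**Step 1. The model as listed.** Let C = 1 for survivors and 0 for controls, M = baseline muscle mass, t = year. Apart from adjustment covariates:

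E[Y] = b0 + b1·t + b2·C + b3·t·C + b4·M + b5·M·t

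The muscle mass-decline association is the change in the yearly slope per unit of M:

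- controls: b5
- survivors: b5
- difference: b5 − b5 = 0, whatever the data show.

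It makes no difference whether M·t is fitted together with t·C or in a separate model; b5 is common to both groups either way. The coefficient b3 is the group difference in slope at equal muscle mass, which is another quantity.

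**Step 2. The model that contains the target.** Add b6·M·C + b7·M·t·C. The association is then b5 in controls and b5 + b7 in survivors, and the difference is b7. The design matrix goes from rank 6 to rank 8, so the listed terms do not already imply the two new ones.

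**Step 3. What the common coefficient reports.** If M has the same within-group variance in both groups and survivors make up a share p of the sample, the common b5 is about p × (survivor association) + (1 − p) × (control association). Assume, for illustration only, 0.8 in survivors and 0.2 in controls:

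| Assumed p | Common value |
|---|---|
| 0.25 | 0.25 × 0.8 + 0.75 × 0.2 = 0.35 |
| 0.50 | 0.50 × 0.8 + 0.50 × 0.2 = 0.50 |
| 0.75 | 0.75 × 0.8 + 0.25 × 0.2 = 0.65 |

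A simulation with those associations agrees. It used 6000 women, about equal groups, 5 annual measures, standardised M, random-intercept SD 5 and residual SD 4, all assumed except the sample size. The listed model returned 0.49. The extended model returned 0.19 in controls and a difference of 0.61, hence 0.19 + 0.61 = 0.80 in survivors. The year by survivorship coefficient was −0.26 in both models, so in this setting adding the terms did not disturb the answer to the decline hypothesis.

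**Step 4. Cost in precision.** Under the same equal-variance assumption, Var(b7) relative to the variance of the common b5 is 1/[p(1 − p)]. At p = 0.5 this is 4, so the standard error doubles. At p = 0.25 or 0.75 it is 1/0.1875 = 5.33, and the standard error is about 2.3 times as large. The absolute precision cannot be worked out from the article.

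**The case against.** The strongest reply is that the Background clause may not govern. The Abstract, the hypothesis that follows the objectives in the Background, and the Aim 2 hypothesis in the Statistical plan all ask whether survivors decline faster. Year by survivorship answers that, and the article interprets it that way. On this reading the plan is coherent and one loosely worded clause is at fault. This part stands: rewording the Background would be an equally valid repair.

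It can also be said that a condensed article leaves full model specification to the complete protocol, which is not shown, and that the list of terms is not declared exhaustive. This carries less weight. The longitudinal paragraph names its slope terms and interprets each, and the preceding paragraph specifies the survivorship interaction for the cross-sectional models. A survivorship interaction with muscle mass was thus thought worth stating for one half of the aim and is absent from the other. The heterogeneity terms listed by time since diagnosis, site and treatment apply within survivors only and do not fill the gap.

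A reader might go further and infer that the study cannot address Aim 2, or that its decline hypothesis goes untested. The documents do not support that: the cross-sectional half has its interaction and the group difference in decline has its term. Nor do the simulated values measure an error in this study. They rest on assumed associations, and the article gives no evidence that the true associations differ between groups.

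**Conclusion.** The point holds for the functional-decline part of Objective 2 as the Background words it. The listed longitudinal terms fix the group difference in the muscle mass-decline association at zero, so that question cannot be answered with them. The conclusion rests only on reading the listed terms as the model and the Background clause as a real objective; it needs no assumption about effect size.

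How far a pooled association would mislead is unknown, because it depends on how far the groups truly differ and on the group split, and the article gives neither.

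This should be fixed before analysis, but it is not a fatal flaw. Muscle mass, survivorship status and annual function are collected in any case, nothing irreversible depends on the choice, and no planned estimate becomes invalid for the hypothesis it serves.

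**What to change.** First decide which question Aim 2 asks about decline, and make the Abstract and the Background agree.

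- **If the difference in associations is intended:** add muscle mass by survivorship and muscle mass by year by survivorship to the linear mixed model, and name the three-way coefficient as the estimate for the decline part of Objective 2. Fitting the model by group with a formal test of the difference would serve as well. Report the muscle mass-slope association in survivors, in controls, and their difference, each with a 95% confidence interval. Centre baseline muscle mass, so that year by survivorship is read at average muscle mass once the three-way term is present.
- **If only the group comparison is intended:** reword Objective 2 in the Background to say so, and describe muscle mass by year as an association assumed common to both groups.

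The first option costs one sentence and two model terms, with no new data. Its drawback is precision: the three-way term is estimated less precisely than the two-way terms, so it should be presented as an estimate with its interval, and a wide interval should not be read as evidence that the associations are equal.
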